### Assessment of outcome measures

The study measures are described below.

#### Blood pressure measurements

The systolic BP reduction in patients will assessed as follows as mean change in systolic BP from baseline to 12 months. BP readings will be assessed with validated automated BP device as we did in our previous trial [10]. A total of three readings will be taken by trained study coordinators using an automated BP monitor with the patient seated comfortably for 5 min prior to the measurements, following the AHA guidelines [31]. The same procedure will be followed at 6- and 12-month study visits. The average of the 3 BP readings will be used as the measure for each study visit. Uncontrolled BP is defined as average clinic SBP ≥ 140 mmHg or DBP ≥ 90 mmHg following JNC-7 guidelines [31].

#### Mediators of TASSH uptake

The following measures will be used to assess the potential mediators of the adoption of TASSH across the CHPS zones at the systems, organizational, and provider levels.

##### Systems-level and organizational-level measures

*Organizational Capacity for Change* (*OCC*) [32] is a 32-item multidimensional scale that evaluates an organization’s capacity to upgrade or revise existing organizational competencies, while cultivating new competencies that enable the organization to survive and prosper. It comprises different aspects of leadership, employee behavior, and an organizational infrastructure supporting organizational change. Items are rated on a 5-point Likert scale. OCC has a Cronbach *α* of 0.87.

*Implementation Leadership* will be assessed with the Implementation Leadership Scale (ILS) [33] which has excellent reliability, convergent, and discriminant validity. The ILS is a brief 12-item measure with four subscales: Proactive Leadership (*α* = .95), Knowledgeable Leadership (*α* = .96), Supportive Leadership (*α* = .95), and Perseverant Leadership (*α* = .96) and a total score (*α* = .98) [33].

*Implementation Climate* will be assessed with the Implementation Climate Scale (ICS) [34] that measures shared perceptions of the policies, practices, procedures, and behaviors that are expected, supported, and rewarded to facilitate effective evidence-based practice (EBP) implementation. It has an overall Cronbach’s alpha of .91 (18 items, 3 items on each subscale). The six subscales of EBP Implementation Climate are as follows: Focus on EBP (*α* = .91), Educational Support for EBP (*α* = .84), Recognition for EBP (*α* = .88), Rewards for EBP (*α* = .81), Selection for EBP (*α* = .89), and Selection for Openness (*α* = .91) [34].

*Organizational Culture domain (i.e., Proficient Culture) of the Organizational Social Context Scale* [35] is a 15-item proficiency subscale that will be used to evaluate the practice capacity proficiency level at participating CHPS compounds. Proficient Organizational Cultures [36] are those characterized by shared norms and expectations that the CHOs place the well-being of each patient first, are skilled service providers, and have up-to-date knowledge of the TASSH protocol. Items are completed using a 5-point rating scale ranging from 1 (never) to 5 (always) with measures such as responsiveness (e.g., “members of my organizational unit are expected to be responsive to the needs of each patient”) and competence (e.g., “members of my organizational unit are expected to have up-to-date knowledge”). Alpha reliability for the proficient culture scale is .89 [35, 36].

##### Provider-level measures

*Evidence-Based Practice Attitude Scale* (*EBPAS*) [37, 38] is a 15-item measure with four subscales that assess attitudes toward adoption of EBP as a function of perceived appeal of EBP, requirements to use EBP, provider openness, and perceived divergence between EBP and usual care. EBPAS total scores (*α* = .76) represent global attitudes toward adoption of EBP. EBPAS responses are scored on a 5-point scale (*0 = Not at all*, *4 = To a Very Great Extent*), and scores are associated with provider-level attributes and organizational characteristics [37, 38].

*Organizational Change Recipients’ Beliefs Scale* [39] is a 24-item tool that evaluates the following: (a) the degree of buy-in among change recipients (the CHOs), (b) deficiencies in specific beliefs that can adversely impact the success of organizational change, and (c) planning and executing actions to enhance buy-in among organizational change recipients. Items are scored on a 5-point Likert scale. The Cronbach *α* ranges from .70 to .94 [39].

#### Sample size and power estimates

The proposed design is a cluster randomized design to compare PF versus usual care. The primary outcome is a composite measure of adoption ratings to assess the degree to which the TASSH protocol is implemented at the CHPS compounds. The secondary outcomes are the difference in the change in systolic BP between patients at the CHPS sites randomized to PF versus those at the usual care CHPS sites. The unit of randomization is the CHPS compound, and the total sample size is the average number of CHOs at the CHPS sites who will provide the adoption ratings (primary outcome) at each site × the number of CHPS compounds and the average number of patients whose systolic BP will be assessed (secondary outcome) enrolled at each CHPS compound × the number of CHPS compounds. In order to estimate the number of CHPS compounds and the average number of CHOs and the average number of patients needed to have power of .80 for a hypothesis test with a type 1 error rate (alpha) of .05, we have assumed a moderate standardized effect size (*d*) of .50 of the difference in change in adoption ratings between the CHOs in the CHPS sites in the UC group versus those in the CHPS sites in the PF group from baseline to 12 months. We note that Baskerville et al. reported in a systematic review of practice facilitation in primary care settings an average effect size of *d* = .56 [15]. We also calculated the sample size for an assumed degree of dependency (intra-cluster correlation—ICC) of the CHOs’ data within CHPS compounds of .10. Thus, for an ICC of .10 and 2 CHOs providing the adoption ratings, our target number of CHPS compounds to recruit is 70. As such, a total of 140 CHOs will participate in this study. For the secondary outcome of patient change in systolic BP, we will have substantially greater power than .80 under the same effect size (*d* = .50) and ICC assumptions as we anticipate enrolling an average of 10 patients/compound. So, with 70 compounds, we would enroll 700 patients. Aim 3 concerns the correlation relationship between different mechanisms of change and the change in adoption ratings between baseline and 12 months. For this analysis, we will have the entire sample of 70 compounds and 140 nurses. With this sample and the same assumptions that we made for aim 2a and aim 2b, we will have power of .80 to detect a moderate correlation of .30. Finally, aim 4 concerns detecting a quadratic pattern consistent with sustainability across the baseline and 12- and 24-month time points. Again, the entire sample will be available for this analysis. The standardized effect size for the quadratic effect will depend considerably on the exact form of the quadratic pattern. The largest effect size would occur when the adoption is not sustained; that is when the adoption ratings revert to their baseline values after PF has ended. With the proposed sample size, we will have power greater than .90 to determine if this unwelcome event occurs.

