
#### Analysis for aim 2a: The adoption of TASSH will be higher in the CHPS compounds randomized to the PF strategy than those in usual care at 12 months post-randomization

This analysis will be accomplished with a multilevel mixed model using an unstructured covariance matrix across two time points, baseline and 12 months. The analysis will have one within-person factor—time (baseline and 12 months coded naturally as months 0 and 12)—and one primary between-patient factor (randomization group dummy coded as 0 = UC and 1 = PF). Fixed effects will be specified for time, randomization group, and their interaction effect (group by time). The outcome measure will be a composite index for adoption of TASSH (defined as rate of identification of HTN, rate of lifestyle counseling for patients with HTN, and medication referral for patients with HTN). Additionally, the CHOs will be nested within compounds creating a 3-level analytic model (observations nested within CHOs nested within compounds). Random effects will be specified for CHPS and for CHO, adjusting for the clustering of measures within CHO and CHO within CHPS. Multilevel modeling software (SAS, version 9, PROC MIXED) will be used to compute full information maximum likelihood (FIML) estimates of the model parameters. The PROC MIXED procedure will use an error structure that allows for the possibility of group differences in (a) the error variances at 12 months and (b) the serial correlations of the baseline with the 12-month outcomes. The primary test is the group × time interaction, and the resulting *F* test will provide the primary “intent to treat” test of the hypothesis. If this is statistically significant at the two-tailed *α* = .05 level, for ease of interpretation, we will estimate and report the magnitude of the treatment effect, with 95% CI for adoption. Ideally, the randomization of participants to treatment groups will obviate the need for any covariates in the analysis. However, in the event that baseline differences between the patients in each group on the outcomes, demographic, or secondary measures are found, those variables will be included as covariates in the model (including their interactions with time).

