#### Analysis for aim 3: Sustainability of TASSH will be higher at the CHPS zones randomized to PF than those in CHPS zones randomized to usual care at 24 months post-randomization

Sustainability will be defined as adoption of TASSH at 24 months (12 months following the completion of the intervention). As in aim 2a, this analysis will be conducted at the level of the CHO. The analysis will be accomplished with a multilevel mixed model using an unstructured covariance matrix across two time points, baseline and 24 months post-randomization. Fixed effects will be specified for time, group, and group by time. Random effects will be specified for CHO and CHPS to account for the clustering of measurements.

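### The power of more than .90 to determine whether adoption reverts after facilitation ends belongs to a quadratic test that cannot identify reversion, and the planned sustainability analysis does not use that test

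*Protocol article*

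**What the plan says.** In the protocol article, the section on sample size and power estimates ends with sustainability: "aim 4 concerns detecting a quadratic pattern consistent with sustainability across the baseline and 12- and 24-month time points". (It numbers this aim 4. The objectives and the analysis sections call sustainability aim 3.) It continues: "The largest effect size would occur when the adoption is not sustained; that is when the adoption ratings revert to their baseline values" after facilitation stops. It concludes that, with the planned sample, "we will have power greater than .90 to determine if this unwelcome event occurs".

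The section on the analysis for aim 3 takes another route: "Sustainability will be defined as adoption of TASSH at 24 months (12 months following the completion of the intervention"). The model there is a group-by-time analysis on two occasions only, baseline and 24 months. Sustainability also appears as a secondary outcome in the section on study outcomes.

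**The concern.** The power section reads one test result in two opposite ways. A detected quadratic is said to be consistent with sustainability, and it is also how the trial would establish that adoption was not sustained. If the test responds both to a plateau and to a collapse, then the figure above .90 is the chance of seeing curvature and not the chance of recognising lost adoption. A reader, funder or monitoring board would then believe that the trial can settle what happens in the year after facilitation better than any analysis in the document can.

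**Working it through.** **Inputs from the protocol.**
- 70 compounds, 2 community health officers (CHOs) each, intra-cluster correlation .10 (sample size section); 35 compounds and 70 CHOs per arm (section on masking and blinding).
- "type 1 error rate (alpha) of .05". The test is two-sided for aim 2a ("If this is statistically significant at the two-tailed" level), assumed to carry over.
- Sample size "needed to have power of .80 for a hypothesis test", with a standardized effect "of .50 of the difference in change in adoption ratings between the CHOs in the CHPS sites in the UC group" versus the facilitation group.

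**Not stated, so assumed.** The quadratic is compared between arms, d is in SDs of the 0-to-12-month change, and the three occasions are equally correlated. Other structures follow in step 4.

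**1. Reproduce the sample size.** Independent CHOs needed per arm: 2 × (1.960 + 0.842)² / 0.50² = 62.8, so 63. The design effect is 1 + (2 - 1) × 0.10 = 1.10, and 63 × 1.10 = 69.3 CHOs per arm. At 2 CHOs per compound and two arms, that is 69.3 compounds, against 70 stated. The effective number per arm is 70 / 1.10 = 63.6, and power at d = .50 is .805 (normal) or .794 (t, 68 df). The main calculation holds.

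**2. The contrast.** For equally spaced times the quadratic contrast is Y0 - 2·Y12 + Y24. Between-arm patterns give:
- no change (0, 0, 0): 0
- continued straight-line gain (0, d, 2d): 0
- fully sustained (0, d, d): -d
- half lost (0, d, d/2): -1.5d
- fully reverted (0, d, 0): -2d

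The sign is the same from plateau to collapse. The size does not identify the pattern either: a fully sustained effect of 1.0 and a fully reverted effect of .50 both give -1.0. This step needs no assumption about correlation.

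**3. Rejection rates.** Under equal correlation ρ and occasion variance σ², a change score has variance 2σ²(1 - ρ) and the quadratic has 6σ²(1 - ρ), three times as much. The effect size is |contrast| / √3, and the test statistic is centred at effect size × √(63.6 / 2) = effect size × 5.64. For full reversion the effect size is 1.0 / 1.732 = .577, centred at 3.26, and power is Φ(3.26 - 1.96) = .903. This reproduces the protocol's figure.

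| True pattern, d = .50 | Quadratic, normal | Quadratic, t (68 df) | 12-to-24-month change, normal | Baseline-to-24-month change, normal |
|---|---|---|---|---|
| Straight-line gain | .05 | .05 | .805 | 1.00 |
| Fully sustained | .370 | .362 | .05 | .805 |
| Half lost | .685 | .673 | .292 | .292 |
| Fully reverted | .903 | .894 | .805 | .05 |

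The straight-line pattern rejects the 12-to-24-month contrast because adoption is still rising. A simulation of 20,000 trials per pattern with 35 compounds per arm gave .36, .67 and .89 for the quadratic under the last three patterns.

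**4. Other correlation structures.**
- AR(1) with ρ from .3 to .7: sustained .40 to .46, reverted .93 to .96.
- d in SDs of a single occasion, ρ from .3 to .7: sustained .28 to .56, reverted .79 to .99.
- Quadratic tested within the facilitation arm alone (equal correlation): sustained .63, reverted .996.

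**5. Precision of a direct contrast.** The 95% CI half-width for the between-arm 12-to-24-month change is 1.996 × √(2 × 1.10 / 70) = 0.354 SD of change.

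**The case against.** The strongest reply is that the statistical methods never run this test. The aim 3 analysis uses two occasions, from which no quadratic can be estimated. With equal correlation, it rejects in about 80% of trials if d = .50 is fully sustained and in 5% if adoption fully reverts. This stands. A reader might infer that the trial's own analysis would flag sustained adoption as a failure in more than a third of trials; the document does not support that.

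A reader might also take the 36-37% as a type I error inflated about sevenfold. It is not. The protocol never makes absence of loss the null hypothesis. It says that the effect size depends on the form of the pattern and that reversion gives the largest effect, which already leaves room for a plateau as a smaller departure. The figure is power against one alternative, and non-rejection remains the likelier result for a plateau at d = .50 in the base case. Nor is the null only continued growth: it is any straight line, including no change.

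The protocol states no rule that significance alone means loss, and the estimated means would show the shape. That is fair, but the conclusion would then rest on the means, and the stated power would not apply to it. The correlation between occasions is indeed not given, so the source of the figure above .90 is inferred. The signs in step 2 do not depend on it.

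The reply does not rescue the claim itself. The aim 3 model leaves out month 12, so an effect gained and lost looks the same as an effect that never occurred: both give a non-significant result.

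**Conclusion.** Wrong as written, and confined to the power statement for a secondary aim. The sample size, the primary outcome and the planned aim 3 analysis are not affected by the quadratic. The figure above .90 can be reproduced, so the arithmetic is not the fault. The fault is the purpose attached to it: it is at best the chance of seeing curvature under complete reversion, and no analysis in the document gives that power to identify reversion. A contrast that does separate a plateau from a loss has power of about .80 for complete reversion and about .29 if half the effect is lost. These rates rest on d = .50 in SDs of change, a two-sided .05 test and equal correlation between occasions. That a plateau and a reversion both lie in the alternative, with the same sign, rests on none of these.

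**What to change.** Delete the quadratic and the figure above .90 from the sample size section. State instead the power of the test planned for aim 3: about .80 for a sustained d of .50, with the assumed correlation named.

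If the trial wants to keep a claim about detecting reversion, amend the sample size section and the aim 3 analysis together, since changing only one leaves the powered and the planned tests mismatched. Fit one model to baseline, 12 and 24 months. Report the between-arm 12-to-24-month change with its 95% CI (expected half-width about 0.35 SD of change) beside the 24-month difference. Restate power as about .80 for complete reversion and about .29 for loss of half the effect. Say that a non-significant 12-to-24-month change will not be read as proof of sustainability, and that the confidence limit for the loss is what will be interpreted.

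The cost is wording and, in the second case, one contrast from data already planned. No visits or participants are added. The drawback is a less favourable stated power.

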#### Analysis for aim 4: Inner setting variables (implementation climate, leadership support, organizational capacity) will mediate the effect of PF on adoption of TASSH at 12 months following randomization and sustainability at 24 months following randomization

In this analysis, we will evaluate the mediators of adoption and sustainability of the PF implemented TASSH program. In particular, we will assess the extent to which inner setting variables (e.g., implementation climate, leadership engagement, and organizational capacity) affect the degree of adoption of TASSH at 12 months utilizing structural equation modeling techniques. We will estimate a just-identified path model using the robust weighted least squares estimator to investigate relationships among the theoretical mediators of implementation climate, leadership engagement, and organizational capacity. Based on our conceptual model, we will test the direct effects from the theoretical constructs to adoption. In addition to the direct effects, the indirect effects from the PF intervention to adoption via inner setting variables will be estimated as the product of component direct effects and tested using bootstrapped 95% confidence intervals. As with previous models, random effects will be specified for CHPS and participant to account for the clustered nature of measurements.

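### The power above .90 quoted for sustainability belongs to a three-time-point quadratic that the planned baseline-versus-24-month analysis cannot estimate; the mediation power likewise covers at most one leg of the planned indirect-effect test.

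*Protocol article*

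**What the plan says.** **Sustainability, power.** Protocol article, Sample size and power estimates: "aim 4 concerns detecting a quadratic pattern consistent with sustainability across the baseline and 12- and 24-month time points". The largest effect is said to arise when adoption returns to its baseline value after facilitation ends, and for that case "we will have power greater than .90 to determine if this unwelcome event occurs".

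**Sustainability, analysis.** Analysis for aim 3 specifies a multilevel mixed model with an "unstructured covariance matrix across two time points, baseline and 24 months post-randomization". The fixed effects are time, group and group by time. Sustainability is defined there as adoption at 24 months, and the hypothesis is that it is higher under practice facilitation (PF) than under usual care (UC).

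**Mediation, power.** The power section, under the label Aim 3, considers the correlation between mechanisms of change and change in adoption, and says "we will have power of .80 to detect a moderate correlation of .30" with 70 compounds and 140 nurses.

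**Mediation, analysis.** Analysis for aim 4: "the indirect effects from the PF intervention to adoption via inner setting variables will be estimated as the product of component direct effects", tested with bootstrapped 95% confidence intervals. It also tests the direct paths from the mediators to adoption.

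**Labels.** In Objectives and in both analysis sections, Aim 3 is sustainability and Aim 4 is mediation. The power section has them the other way round.

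**The concern.** A power statement is useful only if it describes the test that will be run. A quadratic needs at least three time points and the planned model has two. The two tests also respond in opposite directions: between full retention and full reversion, the quadratic gains power as the 12-month effect is lost, while the 24-month group-by-time test gains power as it is kept. The article thus claims strong protection against overlooking a loss of adoption, but specifies a model that contains no test of that loss. If this stands until the 24-month data are in, the team would have to choose after the fact between two tests that answer different questions.

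The mediation statement has a milder form of the same fault. A correlation between mediator and adoption speaks to one leg of a product of two paths.

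**Working it through.** **Inputs from the article.** "power of .80 for a hypothesis test with a type 1 error rate (alpha) of .05"; two-sided testing, from "statistically significant at the two-tailed" in Analysis for aim 2a and assumed to carry over; standardized effect "of .50 of the difference in change in adoption ratings between the CHOs" from baseline to 12 months; ICC .10; 2 CHOs in each of 70 compounds, 70 CHOs per arm; very little missing data expected for the adoption ratings.

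**Step 1: reproduce the primary sample size.** n per arm = 2(1.960 + 0.842)²/0.50² = 62.8, so 63. The design effect is 1 + (2 − 1)(.10) = 1.10. Then 63 × 1.10 = 69.3 CHOs, which is 35 compounds per arm and 70 in total. This reproduces. Effective n per arm is 70/1.10 = 63.6, and the standard error of a standardized difference is √(2/63.6) = 0.177.

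**Step 2: reproduce the power above .90.** Apply the contrast (1, −2, 1) to PF−UC differences of (0, .50, 0), which is full reversion. The effect has size 1.0. *Assumptions:* d is per SD of change and correlations between visits are equal. With SD(change) = 1 the contrast variance is 3, the standardized effect is 1/√3 = .577, and .577/0.177 = 3.26. Power is .90 (normal) or .89 (t, 68 df). The stated figure is thus reproduced, within rounding, for a three-time-point quadratic. If d were per raw SD instead, power would be .63, .79, .90 and .99 for between-visit correlations of 0, .3, .5 and .7.

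**Step 3: the planned test.** Group by time over 0 and 24 months, same SD of change. With full retention, .50/0.177 = 2.82, giving power .81 (normal) or .79 (t). Normal approximation by share of the 12-month effect retained:

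| Retained | Planned 0 vs 24 test | Quadratic | Change from 12 to 24 |
|---|---|---|---|
| 0% | .05 | .90 | .81 |
| 25% | .11 | .81 | .56 |
| 50% | .29 | .69 | .29 |
| 75% | .56 | .53 | .11 |
| 100% | .81 | .37 | .05 |

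The last column uses a difference of .50 × (1 − share retained) with the same SD, under the assumptions of Step 2. The quadratic rejects 37% of the time even when nothing is lost, because a rise followed by a plateau is also curved. It is therefore not specific to reversion.

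**Step 4: the correlation.** Fisher z: power = Φ(0.3095 × √(N − 3) − 1.960), where atanh(.30) = 0.3095.
- N = 140/1.10 = 127: .93
- N = 140, clustering ignored: .95
- N = 70 compounds: .72
- N needed for .80: (2.802/0.3095)² + 3 = 85

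No stated sample gives .80.

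**Step 5: the indirect effect.** The article gives no PF-to-mediator effect, so d = .3, .5 and .8 are assumed, with a partial r of .30 for mediator to adoption. Joint-significance power is the product of the two path powers; at N = 127 and d = .5 it is .805 × .93 = .75.
- Effective N = 127: .37, .75, .93
- Compound-level mediator, CHO-level ratings (simulated): about .2, .5 and .85
- N = 70, compound means throughout: .17, .39, .65

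Simulated percentile bootstraps agree with the first and third rows to within about .02.

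**The case against.** **The two tests have different hypotheses.** A reader might set 5% against the claimed 90% and conclude that the planned test has lost nearly all its power. That does not follow. Analysis for aim 3 asks whether adoption is higher under PF at 24 months. Under full reversion that null is true, so 5% is the correct type I error. For its own question the planned test is about as well powered as the primary one. The fault is that the power section describes another test.

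**No decision rule is stated.** A reader might infer that a non-significant 24-month result will be taken to mean that adoption was not sustained. The article does not say so. Nor is the design unable to show loss of adoption: adoption is assessed at 12 and 24 months in both arms, and Aim 2a estimates the change from 0 to 12 months. Only the Aim 3 model leaves month 12 out. One caution remains: Aim 2a makes reporting of the effect size conditional on significance, and Analysis for aim 3 does not say whether that carries over.

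**Mediation.** The .80 is claimed for a correlation, never for the indirect effect, and the direct mediator-to-adoption paths are also tested. The correlation is therefore partly relevant, and at CHO level .80 is conservative. Replacing it with a fixed range such as .4 to .75 would put into the protocol a figure that rests on an unstated PF-to-mediator effect of d = .50.

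All of this stands. It narrows the point but does not remove it: no analysis section of the article supplies a three-time-point model, and an unseen analysis plan cannot agree with both sections as written.

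**Conclusion.** The contradiction holds. Power above .90 is claimed for a quadratic over three time points, and the specified model has two. On the article's own inputs the planned test has power of about .79 to .81 if d = .50 is fully retained and .28 to .29 if half is retained. It is not a test for detecting reversion. The quadratic figure of .89 to .90 rests on d being per SD of change and on equal correlations between visits.

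The labels of Aims 3 and 4 are swapped in the power section. The .80 for r = .30 is not reproduced (.93 or .72 by the level taken), and it covers at most the mediator-to-adoption path. Power for the indirect effect runs from roughly .2 to .9 over assumed PF-to-mediator effects of d = .3 to .8 and different mediator levels; the article fixes neither.

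This should be fixed, but it does not threaten the trial. Both aims are secondary, the 70-compound calculation for the primary outcome reproduces, and the documents do not support calling the planned 24-month test invalid.

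**What to change.** 1. **Sustainability.** Preferably fit Aim 3 to baseline, 12 and 24 months. Report, with 95% confidence intervals and whatever the significance, the PF−UC contrast at 24 months and the PF−UC difference in change from 12 to 24 months. State power for these contrasts: under the assumptions above, about .79 to .81 for the first if the effect is fully retained and for the second if it is fully lost. At minimum, withdraw the claim of power above .90 and state the power of the 0-versus-24-month test.
2. **Labels.** Renumber Aims 3 and 4 in the power section to match Objectives and the analysis sections.
3. **Mediation.** Say that the r = .30 figure refers only to the mediator-to-adoption path, and recompute it for a declared level of analysis. Then either give indirect-effect power over a declared range of PF-to-mediator effects and mediator levels, or label the mediation analysis exploratory.

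The cost is wording in the protocol and analysis plan, settled before the 24-month data are seen. The assessments at all three time points are already planned, so no data collection, randomization or primary inference changes. The stated power for sustainability becomes less favourable, and that for mediation becomes explicitly dependent on assumptions.
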